| Data/ Statistical Analysis For all parts of the study, the population will be people with new-onset type 2 diabetes in CPRD from 2006 (see section K, above) and the exposure will be ethnicity (either South Asian vs. European [baseline] or African Caribbean vs. European [baseline], as detailed in section L, above). Covariates in base models will include age and sex, and further covariates will be considered individually, as outlined in section vi) below. Statistical analysis is further considered by objective:   1. **Outcome**: time to initiation of first-line anti-diabetic medication, probability of receiving anti-diabetic 1 year post-diagnosis   **Entry**: date of type 2 diabetes diagnosis  **Exit**: date of first anti-diabetic prescription (defined by the absence of a prescription for the medication in the previous 6 months’ records), or end of study/ leaving CPRD practice/ death  **Analysis**: summary statistics will be compared by ethnicity using Kaplan-Meier time-to-event analysis (cumulative failure probability in a given time frame by ethnicity, comparison of medians by log-rank test), Cox proportional hazards regression models will be used to adjust for confounding/ investigate potential mediators  **Example effect measure**: hazards ratio (HR) for anti-diabetic prescription   1. **Outcome:** proportions of patients prescribed medication from each anti-diabetic (stratified by first- to third-line treatment), antihypertensive and lipid-lowering class (defined by the absence of a prescription for the medication in the previous 6 months’ records)   **Sub-population:** a) all participants starting first- to third-line anti-diabetic treatment, b) all patients on antihypertensives, or c) all patients on lipid-lowering medication  **Analysis:** proportions receiving each drug will be compared by ethnicity, then logistic regression models will be used to adjust for confounding/ investigate potential mediators  **Example effect measures**: odds ratio (OR) of being prescribed metformin (=1) vs. non-metformin medication (=0) at first stage of treatment, OR of being prescribed sulphonylurea (=1) vs. non- sulphonylurea medication (=0) at second stage of treatment, OR of calcium-channel blocking antihypertensive prescription vs. non- calcium-channel blocking antihypertensive in those on antihypertensive treatment, OR of statin prescription vs. non-statin lipid-lowering medication prescription in those with >10% 10 year cardiovascular risk   1. **Outcome:** proportions of patients prescribed each dose of each anti-diabetic, antihypertensive and lipid-lowering medication, stratified by treatment stage (defined by the absence of a prescription for the medication in the previous 6 months’ records)   **Sub-population:** a) all participants on first- to third-line anti-diabetic treatment, b) all patients on antihypertensives, or c) all patients on lipid-lowering medication  **Analysis: :** proportions receiving each dose of each drug will be compared by ethnicity, then logistic regression models will be used to adjust for confounding/ investigate potential mediators  **Example effect measures**: OR of being prescribed maximum dose (2g daily) vs. sub-maximum dose of metformin, OR of being prescribed atorvastatin 10mg per day vs. higher doses (20mg, 40mg or 80mg)   1. **Outcome:** yearly monitoring rate post commencement of medication from each anti-diabetic (first- to third-line), antihypertensive and lipid-lowering class – i.e. number of times HbA1c/ blood pressure/ blood lipids measured per person-year of follow-up, stratified by year after commencement; may be multiple entry dates per person for different medications   **Entry:** first use of any medications of interest from 2006 onwards  **Exit:** first of; end of strata (e.g. 1 year after medication commencement), end of study/ leaving CPRD practice/ death  **Analysis:** summary statistics will be compared by ethnicity, Poisson regression modelling used to adjust for confounding/ investigate potential mediators  **Example effect measures**: yearly monitoring rate ratios (RRs)   1. **Outcome:** time to medication intensification (up-titration, addition or switching) after detection of sub-optimal control of diabetes, hypertension or blood lipids, or probability of intensification 1 year post-detection of sub-optimal control; may be multiple entry dates per person for different medications   **Entry:** date when sub-optimal risk factor control detected (see section M for how this is defined for each risk factor)  **Exit:** first of; date of anti-diabetic, antihypertensive or lipid-lowering treatment intensification, end of study/ leaving CPRD practice/ death  **Analysis:** summary statistics will be compared by ethnicity using Kaplan-Meier time-to-event analysis (cumulative failure probability in a given time frame by ethnicity, comparison by log-rank test), Cox proportional hazards regression models will be used to adjust for confounding/ investigate potential mediators  **Example effect measures**: cumulative failure probability for each ethnic group 1 year post detection of sub-optimal value, comparison of median survival times using the log-rank test by ethnicity, HRs of intensification stratified by year   1. **Outcome:** influence of deprivation, polypharmacy, multi-morbidity, drug adherence (iv) and v) only), patient engagement with healthcare, diabetes duration and HbA1c on any ethnic differences found in i) to v).   **Entry:** as above for i), iv) and v)  **Exit:** as above for i), iv) and v)  **Analysis:** as above for i) to v)  **Covariates:** smoking status, BMI, deprivation, polypharmacy, multi-morbidity, drug adherence, patient engagement with healthcare, diabetes duration and HbA1c  **Effect measures:** we will observe the degree of attenuation of the ethnic difference effect measure for each outcome when each covariate is inserted in turn to models, and thus evaluate the likelihood of confounding or mediation  Sub-group/ sensitivity analyses  Analyses will be stratified by age group, and changes in guidelines and temporal trends in drug usage will be accounted for by stratifying by time.  Three sensitivity analyses will be performed – all to boost ethnicity ascertainment. Firstly, on the 58% of CPRD participants with linked secondary care data from Hospital Episode Statistics (HES) (19), using ethnicity codes from HES - present in 78% (18). Secondly, on new registrants since 2006, 78% of whom have ethnicity codes recorded (19). Thirdly, on patients from practices in the London area; where previous research indicates ethnicity recording to be approaching 60% (28).  Plans for addressing misclassification and bias  ­Plans for addressing misclassification of diabetes status and ethnicity are given above (see sections K and L respectively).  Selection bias may arise in ethnicity recording, i.e. greater recording for patients from ethnic minorities, and may also vary across time (with greater recording after the introduction of incentives in 2004) and geographically (greater in urban areas with more ethnic diversity (28) than rural ones with less). We plan to address this in three ways, as detailed above under the “sub-group/ sensitivity analyses” heading. NB/ we do acknowledge these approaches may in themselves introduce bias, and thus we will carefully compare baseline characteristics between the sensitivity and primary analysis populations.  Though primary care prescription data are almost entirely computerised, bias may be introduced into the descriptive arms of the study from unrecorded prescriptions issued in secondary care; equally medication started in secondary care and continued in primary care may falsely lengthen times to up-titration. We anticipate little bias in the monitoring outcome, where blood tests and clinical data such as blood pressure (including those recorded in secondary care) are generally automatically entered into notes via specific templates. Additionally, some bias may be present regarding the ascertainment of treatment intensification, where the intervention is non-pharmacological or constitutes referral to another service. Therefore we will also search for codes indicating lifestyle modification advice or referral which are chronologically close to the medication exposure period.  We plan to examine the influence of drug adherence in explaining any associations between ethnicity and prescribing, but this will only be measured by proxy using the proportion of days covered method; we are unable to verify whether prescriptions have been obtained from pharmacies or whether medication has been taken.  Multiple comparisons  As the study will involve multiple comparisons, findings will be interpreted with caution, and attention paid to clinically meaningful effect sizes rather than p values per se. |

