| Study Background The UK’s largest ethnic minority groups, people of South Asian and African Caribbean descent, are disproportionately affected by type 2 diabetes (1), and most types of cardiovascular disease (2). UKPDS (UK Prospective Study of Diabetes) established the importance of tight blood glucose control in reducing CVD complications (3), but research suggests that glucose control is poorer in UK South Asians and African Caribbeans than Europeans (4, 5), despite their greater prevalence of complications (2). Yet the use of anti-diabetic medication in these groups remains understudied. Blood pressure and lipid control is key in reducing CVD risk in people with and without diabetes (6), therefore we will also examine prescribing patterns for antihypertensives and lipid-lowering medication.  UK guidelines recommend metformin as first-line anti-diabetic therapy, with several choices of further agents before insulin use (7). A recent study has reported on the choice of second-line treatments in CPRD (8; ISAC protocol number 16_267), with some indication that people from ethnic minority groups are less likely to receive newer anti-diabetic drugs. However, the influence of key factors such as diabetes duration and adherence to treatment were not accounted for, and the related questions of monitoring frequency and expediency of appropriate treatment intensification were not studied. Moreover, evidence from smaller primary care databases suggests South Asians and African Caribbeans are less likely than Europeans to receive insulin, and more likely to be on a higher number of oral diabetes drugs (5, 9). UK hypertension guidelines advocate calcium-channel blockers (CCBs) as first-line treatment for African Caribbeans, and ethnic differences in monotherapy are established (10), but little examination of ethnic differences in prescribing exists beyond this. Studies from aggregated primary care data indicate that statins may be under-prescribed in areas with large ethnic minority populations (11, 12), but were limited by analysis at area level.  Delay in anti-diabetic treatment intensification is linked to poorer subsequent control (13), but in spite of the poorer diabetic control in ethnic minority groups, ethnic differences in time to intensification have never been studied. Equally, an absence of research on ethnic differences in intensification of antihypertensives exists (14). However, previous research indicates that African Caribbean people are less likely than their white counterparts to be prescribed statins (15), though it is unclear if this is the case for people with diabetes. Additionally, whilst evidence from CPRD indicates that hypercholesterolaemia with high cardiovascular risk is inadequately treated in people with diabetes (16), scrutiny by ethnicity is lacking. |

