| O. Data/ Statistical Analysis For all parts of the study, the population will be people with and without new-onset type 2 diabetes active in CPRD from 2006 (see section K, above) and the exposure will be ethnicity (either South Asian vs. European [baseline] or African Caribbean vs. European [baseline], as detailed in section L, above). Covariates in base models will include age and sex, and further covariates will be considered individually, as outlined in section vi) below. Statistical analysis is further considered by objective:   1. **Outcome:** Proportion of those eligible for primary prevention who are prescribed a) antihypertensives and b) lipid-lowering medication   **Entry:** Date of incident a) hypertension Read code/ raised BP reading or b) elevated 10 year CVD risk score, at least 12 months after study start date of 1^st^ January 2005  **Exit:** First of; date of first antihypertensive/ lipid-lowering medication prescription (defined by the absence of a prescription for the medication in the previous 6 months’ records), end of study, leaving CPRD practice or death  **Analysis:** Proportions receiving antihypertensives/ statin will be compared by ethnicity, then logistic regression models will be used to adjust for confounding/ investigate potential mediators  **Example effect measure:** Odds ratio (OR) of receiving an antihypertensive/ lipid-lowering medication vs. not for each ethnic group of interest, stratified by time period since identification of hypertension/ elevated CVD risk   1. **Outcome**: time to initiation of first-line anti-diabetic/ antihypertensive/ statin, probability of receiving anti-diabetic/ antihypertensive/ statin at one year post-diagnosis/ identification of high CVD risk   **Entry**: date of type 2 diabetes diagnosis/ incident hypertension Read code or raised BP reading/ incident high 10 year CVD risk score recording  **Exit**: date of first anti-diabetic/ antihypertensive/ statin prescription (defined by the absence of a prescription for the medication in the previous 6 months’ records), or end of study/ leaving CPRD practice/ death  **Analysis**: summary statistics will be compared by ethnicity using Kaplan-Meier time-to-event analysis (cumulative failure probability in a given time frame by ethnicity, comparison of medians by log-rank test), Cox proportional hazards regression models will be used to adjust for confounding/ investigate potential mediators  **Example effect measure**: hazards ratio (HR) for anti-diabetic/ antihypertensive/ statin prescription   1. **Outcome:** proportions of patients prescribed medication from each anti-diabetic (stratified by first- to third-line treatment), antihypertensive and lipid-lowering class (defined by the absence of a prescription for the medication in the previous 6 months’ records)   **Sub-population:** a) all participants starting first- to third-line anti-diabetic treatment, b) all patients on antihypertensives, or c) all patients on lipid-lowering medication  **Analysis:** proportions receiving each drug will be compared by ethnicity, then logistic regression models will be used to adjust for confounding/ investigate potential mediators  **Example effect measures**: odds ratio (OR) of being prescribed metformin (=1) vs. non-metformin medication (=0) at first stage of treatment, OR of being prescribed sulphonylurea (=1) vs. non- sulphonylurea medication (=0) at second stage of treatment, OR of calcium-channel blocking antihypertensive prescription vs. non- calcium-channel blocking antihypertensive in those on antihypertensive treatment, OR of statin prescription vs. non-statin lipid-lowering medication prescription in those with >10% 10 year cardiovascular risk   1. **Outcome:** proportions of patients prescribed each dose of each anti-diabetic, antihypertensive and lipid-lowering medication, stratified by treatment stage (defined by the absence of a prescription for the medication in the previous 6 months’ records)   **Sub-population:** a) all participants on first- to third-line anti-diabetic treatment, b) all patients on antihypertensives, or c) all patients on lipid-lowering medication  **Analysis: :** proportions receiving each dose of each drug will be compared by ethnicity, then logistic regression models will be used to adjust for confounding/ investigate potential mediators  **Example effect measures**: OR of being prescribed maximum dose (2g daily) vs. sub-maximum dose of metformin, OR of being prescribed atorvastatin 10mg per day vs. higher doses (20mg, 40mg or 80mg)   1. **Outcome:** yearly monitoring rate post commencement of medication from each anti-diabetic (first- to third-line), antihypertensive and lipid-lowering class – i.e. number of times HbA1c/ blood pressure/ blood lipids measured per person-year of follow-up, stratified by year after commencement; may be multiple entry dates per person for different medications   **Entry:** first use of any medications of interest from 2006 onwards  **Exit:** first of; end of strata (e.g. 1 year after medication commencement), end of study/ leaving CPRD practice/ death  **Analysis:** summary statistics will be compared by ethnicity, Poisson regression modelling used to adjust for confounding/ investigate potential mediators  **Example effect measures**: yearly monitoring rate ratios (RRs)   1. **Outcome:** time to medication intensification (up-titration, addition or switching) after detection of sub-optimal control of diabetes, hypertension or blood lipids, or probability of intensification 1 year post-detection of sub-optimal control; may be multiple entry dates per person for different medications   **Entry:** date when sub-optimal risk factor control detected (see section M for how this is defined for each risk factor)  **Exit:** first of; date of anti-diabetic, antihypertensive or lipid-lowering treatment intensification, end of study/ leaving CPRD practice/ death  **Analysis:** summary statistics will be compared by ethnicity using Kaplan-Meier time-to-event analysis (cumulative failure probability in a given time frame by ethnicity, comparison by log-rank test), Cox proportional hazards regression models will be used to adjust for confounding/ investigate potential mediators  **Example effect measures**: cumulative failure probability for each ethnic group 1 year post detection of sub-optimal value, comparison of median survival times using the log-rank test by ethnicity, HRs of intensification stratified by year   1. **Outcome:** influence of deprivation, polypharmacy, multi-morbidity, drug adherence (iv) and v) only), patient engagement with healthcare, diabetes duration and HbA1c on any ethnic differences found in i) to v).   **Entry:** as above for i), iv) and v)  **Exit:** as above for i), iv) and v)  **Analysis:** as above for i) to v)  **Covariates:** smoking status, BMI, deprivation, polypharmacy, multi-morbidity, drug adherence, patient engagement with healthcare, diabetes duration and HbA1c  **Effect measures:** we will observe the degree of attenuation of the ethnic difference effect measure for each outcome when each covariate is inserted in turn to models, and thus evaluate the likelihood of confounding or mediation  Sub-group/ sensitivity analyses  See section O of original application  Plans for addressing misclassification and bias  See section O of original application  Multiple comparisons  See section O of original application |

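### Anti-diabetic intensification is not analysed by treatment step, so the hazard ratio can mix response to poor control with ethnic differences in step, in an unknown direction

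*Supplement*

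**What the plan says.** In the amendment's section O (Data/ Statistical Analysis), the outcome is "time to medication intensification (up-titration, addition or switching) after detection of sub-optimal control of diabetes, hypertension or blood lipids". Entry is the "date when sub-optimal risk factor control detected (see section M for how this is defined for each risk factor"), and there "may be multiple entry dates per person for different medications". The only stratification given for this outcome is "HRs of intensification stratified by year". The sub-group text, carried over by reference from the original application, adds: "Analyses will be stratified by age group, and changes in guidelines and temporal trends in drug usage will be accounted for by stratifying by time". Base models contain age and sex. The other covariates are entered one at a time and judged by how much the ethnic effect attenuates.

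The same section treats its other anti-diabetic outcomes differently. Choice is stratified by first to third line, monitoring is defined by line, and dose is "stratified by treatment stage". Section L (Definition of the Study population) restricts the cohort to incident diabetes so that treatment stage can be measured more precisely.

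The amendment's Study Background reports lower insulin use in both minority groups than in the European group. It also describes the minority groups as "more likely to be on a higher number of oral diabetes drugs (5, 9").

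**The concern.** Up-titration, addition and switching all depend on what the patient already takes. Someone on one oral agent has different options left from someone on three, or on insulin. If the groups enter at different steps, and the chance of intensification differs by step, the overall HR differs from 1 even when patients at the same step are treated alike.

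The covariates do not repair this. Polypharmacy counts all medications, not agents for the risk factor in question. Diabetes duration and HbA1c are only proxies for step. Because each is entered singly, no model holds step fixed.

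The study hopes to inform prescribing policy. A difference that comes from case mix by step would call for a different response from one that comes from slower action on a raised HbA1c.

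**Working it through.** **Inputs from the plan** (amendment, Feasibility counts and Sample size considerations): first-line starters 120.4K European, 10.5K South Asian, 4.6K African Caribbean; second-line starters 34.4K, 3.0K, 1.3K; one-year intensification 24%, a single figure for all steps; alpha 0.05 (two-sided assumed); power 90% (the table's β=0.90 read as power). The documents give no rates or ethnic mixes by step, so those below are assumptions.

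**1. The plan's detectable HR.** HR = exp[(1.960 + 1.282)/√(E·a(1−a))], where E = 0.24N and a is the minority share.
- South Asian: E = 0.24 × 130,900 = 31,416. With a = 0.5, HR = 1.037.
- African Caribbean: E = 0.24 × 125,000 = 30,000. With a = 0.5, HR = 1.038.

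Both round to the stated 1.04. The actual shares (0.080 and 0.037) give 1.07 and 1.10; that is a separate matter. What counts here is that the calculation uses first-line numbers and one probability, so no step-specific analysis was sized.

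**2. Three-step illustration with no within-step difference.** For step k with one-year probability p_k, the hazard is λ_k = −ln(1−p_k). For a group with step shares w_k, P = Σw_k·p_k, T = Σw_k·p_k/λ_k, and HR = (P/T in the minority)/(P/T in Europeans).

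Worked case: rates of 30/18/8% on one, two, and three or more drugs.
- Europeans 60/28/12: P = 0.180 + 0.0504 + 0.0096 = 0.240, the plan's figure. T = 0.874 and P/T = 0.2747.
- Minority 50/33/17: P = 0.150 + 0.0594 + 0.0136 = 0.223. T = 0.883 and P/T = 0.2526.
- HR = 0.2526/0.2747 = 0.92.

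| Assumed rates by step | European P | Minority 55/30.5/14.5 | Minority 50/33/17 | Minority 45/35/20 |
|---|---|---|---|---|
| 30/18/8% | 24.0% | 0.96 | 0.92 | 0.88 |
| 27/20/16% | 23.7% | 0.98 | 0.96 | 0.93 |
| 24/24/24% | 24.0% | 1.00 | 1.00 | 1.00 |
| 20/28/35% | 24.0% | 1.03 | 1.06 | 1.09 |

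For the 0.92 case, the South Asian SE of log HR is √[1/(10,500 × 0.223) + 1/(120,400 × 0.240)] = 0.0215, so z = −3.9. For African Caribbeans the SE is 0.0318 and z = −2.6. An artefact of that size would be declared significant.

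**3. Adding an insulin step.** Keep 30/18/8%, a European mix of 55/25/10/10 (last figure insulin), and minority mixes of 50/30/15/5, 50/33/12/5 and 55/28/12/5.
- Insulin-step rate 5%: HRs 0.98, 0.99, 1.02.
- Insulin-step rate 30%: HRs 0.92, 0.94, 0.96.

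**4. Two-step cross-check.** Take 24% at step one and a European later-step share of 34.4/(120.4 + 34.4) = 22%, a proxy. The South Asian Cox HRs for a later-step share 5, 10 and 20 points higher are:
- later-step rate 12%: 0.97, 0.94, 0.88
- 16%: 0.98, 0.96, 0.92
- 24%: 1.00 throughout
- 36%: 1.03, 1.05, 1.11

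**5. Precision within a step.** Using second-line starters as a proxy, 24% and actual shares, the detectable HR is 1.13 for 3.0K against 34.4K and 1.21 for 1.3K against 34.4K.

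**The case against.** A reader might infer that minority patients, being on more drugs, will look slower to be intensified. The documents do not support that. They state an imbalance in step, but no gradient of intensification by step. They also state two imbalances, more oral drugs and less insulin, which can offset each other. Sections 2 to 4 of the working show HRs below 1, at 1 and above 1. Reproducing the plan's 24% does not validate any one set of rates, since many sets do so. This part of the objection stands.

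Four further points carry weight.
- Pooling is inferred from silence. Multiple entry dates for different medications would be compatible with medication-specific episodes. But the text does not say that these are analysed by step, and the plan should.
- It is doubtful that people on no drug are in the risk set. Up-titration and switching presuppose a drug, adherence is a covariate for this objective, and untreated people have their own initiation objective. One sentence would settle it.
- The cited ethnic difference concerns diabetes drugs only. Nothing comparable is cited for the number of antihypertensive or lipid-lowering agents.
- Step lies downstream of ethnicity and earlier prescribing, so it can be regarded as a mediator, and the overall HR is a legitimate contrast. This is a reason to keep the overall HR, not to omit the step-specific one. The plan sets out to examine confounding and mediation, and step is missing from its list.

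Polypharmacy, duration, HbA1c and calendar time give partial control, but none fixes the number of anti-diabetic agents.

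**Conclusion.** The omission holds for anti-diabetic intensification: no entry condition, stratum or covariate captures treatment step, in a plan that uses line or stage for its other anti-diabetic treatment outcomes and itself reports ethnic differences in step. The HR and one-year probability can therefore combine step mix with response to sub-optimal control.

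The size is uncertain and the sign unknown. The three-step illustrations run from about 0.88 to 1.09. They rest wholly on assumed rates and mixes and are not bounds. Several exceed the plan's claimed detectable HR of 1.04; others show little or no bias. For antihypertensive and lipid-lowering drugs the same mechanism is possible, but the plan gives no evidence of an imbalance. This should be fixed as a cheap improvement; confidence is moderate.

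**What to change.** In section O, under time to intensification:
- Keep the age- and sex-adjusted overall HR, described as the total ethnic contrast.
- Add Kaplan-Meier curves and a Cox model with the baseline hazard stratified by number of anti-diabetic agents at entry (one, two, three or more; insulin separately). Report step-specific HRs beside the stratified overall HR.
- As a check, do the same by number of agents for antihypertensive and lipid-lowering drugs.
- State that people on no drug for the risk factor belong to the time-to-initiation objective.

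The cost is wording and some programming, since step at entry comes from the prescription files already in use. The downside is imprecise African Caribbean estimates at later steps: the proxy above gives a detectable HR of about 1.21 at second line, and third line would be weaker still. Those estimates should be read with their confidence intervals.

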| Plan for addressing confounding Age and sex will be adjusted for in all analyses as potential confounders of associations between ethnicity and prescribing. The potential mediating influences of smoking, BMI, polypharmacy, multimorbidity, patient adherence, patient engagement, diabetes duration and HbA1c will be quantified by adjusting regression models for each of these variables in turn. |
| Plans for addressing missing data Monitoring and treatment of type 2 diabetes is incentivised by the UK’s primary care Quality Outcomes Framework (QOF), therefore recording of cardiovascular risk factors and some other of the covariates mentioned above is likely to be more complete than for other disease areas. Where these factors are missing, we will use complete case analysis as data may not be missing at random.  Missing ethnicity data is the chief concern. Given that ethnicity data are unlikely to be missing at random, multiple imputation methods are not appropriate, and we will perform complete case analysis instead. Complete case analysis will be unbiased if missingness is independent of the outcome, conditional on model covariates. One of the main reasons that missingness would be expected to be associated with prescribing patterns is that people who are poorly engaged with their GP may be less likely to have ethnicity recorded (whatever their ethnicity), or be eligible to be prescribed medication. However, as discussed above we plan to adjust for number of consultations in the year prior to diagnosis. Within those with similar levels of GP contact prior to diabetes diagnosis, it is less conceivable that missingness of ethnicity will be strongly associated with prescribing patterns. Additionally, three sensitivity analyses (see section N) will be performed to boost ethnicity recording. |
| Patient or user group involvement (if applicable) A study steering group will be convened consisting of the collaborators and several people with type 2 diabetes, ideally representing each ethnic group. These individuals will be recruited from the pool of participants from the SABRE study (Southall and Brent Revisited, PI: NC) and will meet annually to discuss the study progress, results and dissemination of findings. Key results will be reported via the media, Diabetes UK website, Living with Diabetes events and “Balance” magazine (for Diabetes UK members), to make people with diabetes aware of the findings. |

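### One-year probabilities of starting or intensifying treatment are outcomes, but only unadjusted Kaplan-Meier by ethnic group is named to estimate them, although the plan says age and sex are adjusted for in all analyses

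*Supplement*

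**What the plan says.** The 2019 amendment, section O (Data/ Statistical Analysis), names a one-year probability among the outcomes of both time-to-event objectives. For initiation it is the "probability of receiving anti-diabetic/ antihypertensive/ statin at one year post-diagnosis/ identification of high CVD risk"; for intensification it is the "probability of intensification 1 year post-detection of sub-optimal control". For intensification the list of example effect measures also opens with the "cumulative failure probability for each ethnic group 1 year post detection of sub-optimal value". For initiation the only example effect measure is the hazard ratio.

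The method is the same for both: "summary statistics will be compared by ethnicity using Kaplan-Meier time-to-event analysis (cumulative failure probability in a given time frame by ethnicity", with a log-rank test. Then "Cox proportional hazards regression models will be used to adjust for confounding/ investigate potential mediators". On covariates, section O says: "Covariates in base models will include age and sex, and further covariates will be considered individually". No predicted, standardised or weighted probability is described.

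The original application's Plan for addressing confounding, which the amendment as shown does not replace, states: "Age and sex will be adjusted for in all analyses as potential confounders of associations between ethnicity and prescribing".

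The original sub-group and sensitivity section, which the amendment keeps by reference, adds: "Analyses will be stratified by age group". It gives no age bands and no pooled estimate, and it does not mention sex.

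**The concern.** A Kaplan-Meier curve drawn by ethnic group describes that group with whatever age and sex mix it has. If the groups differ in age, and age affects how soon a drug is started or stepped up, the one-year probabilities will differ even when patients of the same age and sex are treated alike. The Cox model deals with this for the hazard ratio but, as written, produces no adjusted probability. A listed outcome is thus left without the adjustment promised for all analyses.

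The mediation objective has the same gap. It intends to watch the ethnic effect measure attenuate for every outcome as covariates enter the models, and a Kaplan-Meier probability has no model for a covariate to enter.

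The documents give some reason to take age seriously. The limitations section treats age as a factor that can relax HbA1c, blood pressure and lipid targets. Section L excludes non-specified diabetes up to age 40 in Europeans but only up to 35 in the other two groups, so people aged 36 to 40 with that coding can enter only in the minority groups.

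The original application says interpretation will rest on clinically meaningful effect sizes rather than p values. That gives the absolute probabilities weight in the reading of the results.

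**Working it through.** **Inputs from the plan (amendment, sample size section and Table 1).** One-year anti-diabetic initiation 42%; one-year intensification 24%; 10.5K South Asians or 4.6K African Caribbeans against 120.4K Europeans; α = 0.05 (taken as two-sided); 0.90 (printed as β, read as power). So z = 1.960 + 1.282 = 3.2415.

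**The plan's own figures.** Table 1 gives detectable hazard ratios of 1.03 (initiation) and 1.04 (intensification) for both comparisons. Schoenfeld's formula is HR = exp(3.2415 / √(E·a·(1−a))), where E = N × one-year probability and a is the minority share. For initiation, E = 130,900 × 0.42 = 54,978 and 125,000 × 0.42 = 52,500. With a = 0.5 this gives 1.028 and 1.029; for intensification (E = 31,416 and 30,000) it gives 1.037 and 1.038. These round to the stated values. At the actual shares (0.080 and 0.037) the results are 1.052 and 1.078, and 1.070 and 1.105. That is a separate matter. The plan gives no detectable difference for the one-year probabilities.

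**Detectable absolute difference.** d = 3.2415 × √(p(1−p)(1/120,400 + 1/n)), treating the probability as a simple proportion with no censoring:

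| p | n = 10,500 | n = 4,600 |
| --- | --- | --- |
| 42% | 1.6 points | 2.4 points |
| 24% | 1.4 points | 2.1 points |

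**Illustration A: linear age effect, no ethnic effect.** Assume the minority group is younger by a fixed gap and the log hazard rises by a fixed slope per year younger. Then p = 1 − exp(−λ·exp(slope × gap)), with λ = −ln(0.58) = 0.545 for 42% and λ = −ln(0.76) = 0.274 for 24%. Slopes and gaps are assumptions.

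| Slope per year | Gap, years | From 42% | From 24% |
| --- | --- | --- | --- |
| 0.01 | 5 | 43.6% (+1.6) | 25.1% (+1.1) |
| 0.02 | 8 | 47.2% (+5.2) | 27.5% (+3.5) |
| 0.02 | 10 | 48.6% (+6.6) | 28.5% (+4.5) |
| 0.03 | 10 | 52.1% (+10.1) | 31.0% (+7.0) |

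**Illustration B: two age bands, milder.** Assume 40% of Europeans are in the younger band and age-specific probabilities are identical in all ethnic groups, so the standardised difference is zero. Solve for the older-band hazard h in 0.4(1−exp(−h·HR)) + 0.6(1−exp(−h)) = 0.42 or 0.24. The crude difference is then the extra younger share in the minority group times the gap between the band probabilities.

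| Younger v older HR | Extra younger share | Around 42% | Around 24% |
| --- | --- | --- | --- |
| 1.2 | 10 points | 0.6 | 0.4 |
| 1.2 | 30 points | 1.7 | 1.2 |
| 1.5 | 10 points | 1.3 | 0.9 |
| 1.5 | 30 points | 3.9 | 2.6 |

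With no age effect or no age shift, the crude difference is zero. The artefacts in both illustrations overlap the detectable differences. Both concern the anti-diabetic outcomes and age only; sex mix and the hypertension and lipid cohorts were not illustrated.

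**The case against.** The plan can fairly be read as description followed by adjusted comparison. It calls the Kaplan-Meier output summary statistics and then plans Cox models with age and sex in the base model, which is a usual sequence. Stratifying by age group would give age-specific curves. The effect measures are headed as examples, so an adjusted probability is not excluded, and for initiation the probability is not listed as an effect measure at all.

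Much of this stands, and it rules out several stronger readings. A reader might infer that the ethnic comparison is left crude; it is not, because adjusted hazard ratios are planned for both outcomes. A reader might infer that section L's lower age cut-off was set because minority groups develop diabetes earlier; the stated purpose is to reduce misclassified type 1 diabetes, and for people without diabetes a single threshold of 40 years applies to every group. A reader might also infer that the crude probability will contradict the adjusted hazard ratio in direction; nothing in the documents shows this, and the illustrations assume no ethnic effect.

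What the objection does not remove is the mismatch itself. The probabilities sit under Outcome, one is an effect measure, and no adjusted version is specified. Age stratification without bands or a pooled estimate does not supply one, and it leaves sex out. Calling the curves descriptive and limiting the all-analyses statement to the regression models would resolve the wording, but readers would still have no adjusted absolute contrast.

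**Conclusion.** The point holds in a limited form. No age- and sex-adjusted version of the one-year probabilities is specified, contrary to the statement that both are adjusted for in all analyses, so absolute contrasts between ethnic groups could partly reflect age and sex mix. It would go too far to say that age differences do appear as prescribing differences: that needs both an age gap and an age effect on prescribing, and the documents quantify neither.

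The size is therefore unknown. Under the assumed inputs above it is about 1.6 to 10 points around 42%, or about 0.6 to 4 points on the milder set, against detectable differences of 1.6 and 2.4 points. The direction shown rests on the further assumption that younger patients are treated sooner. The adjusted hazard ratios are not affected. This is worth correcting because the remedy is cheap, not because the main comparison fails.

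**What to change.** In section O, for both time-to-event objectives, add age- and sex-standardised one-year probabilities and their differences by ethnicity. One route is to fit the age-sex Cox model with a baseline stratified by ethnicity, predict each person's one-year probability under each ethnic group's baseline, and average over the pooled age-sex distribution. The other is to weight the Kaplan-Meier curves to that distribution. Give bootstrap intervals, resampling patients, since one person may have several entry dates for intensification.

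Use these figures for the ethnic contrasts and label the crude Kaplan-Meier figures as descriptive, so that section O and the confounding section agree.

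The cost is a few lines of code and a sentence or two in section O. Age and sex are already in the base models, so no new data are needed.
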